**CORONAVIRUS DISEASE 2019- USING ASCORBIC ACID AND ZINC  
SUPPLEMENTATION (COVIDatoZ) Research Study  
A RANDOMIZED, OPEN LABEL SINGLE CENTER STUDY**

**Study Synopsis**

|                    |                                                                                                                                                                                                                                                                                                                                                                                                                                                                                                                                                                                                                                                                                                                                                                                                                                                                                                                                                                                       |
|--------------------|---------------------------------------------------------------------------------------------------------------------------------------------------------------------------------------------------------------------------------------------------------------------------------------------------------------------------------------------------------------------------------------------------------------------------------------------------------------------------------------------------------------------------------------------------------------------------------------------------------------------------------------------------------------------------------------------------------------------------------------------------------------------------------------------------------------------------------------------------------------------------------------------------------------------------------------------------------------------------------------|
| Title              | Coronavirus Disease 2019- Using Ascorbic acid and Zinc Supplementation ( CovidAtoZ ) Research Study                                                                                                                                                                                                                                                                                                                                                                                                                                                                                                                                                                                                                                                                                                                                                                                                                                                                            |
| Purpose            | The primary objective of this study is to determine if ascorbic acid (vitamin C) and zinc gluconate result in shortening the duration and type of symptoms and prevention of hospitalizations in patients with confirmed new diagnosis of coronavirus disease 2019 (COVID-19)                                                                                                                                                                                                                                                                                                                                                                                                                                                                                                                                                                                                                                                                                                         |
| Design             | A prospective, open label four arm study (1. Zinc only 2. Zinc and ascorbic acid 3. Ascorbic acid only 4. Standard of care. All subjects will receive the supplements for 10 days after positive test result                                                                                                                                                                                                                                                                                                                                                                                                                                                                                                                                                                                                                                                                                                                                                                          |
| Number of Subjects | 520                                                                                                                                                                                                                                                                                                                                                                                                                                                                                                                                                                                                                                                                                                                                                                                                                                                                                                                                                                                   |
| Inclusion Criteria | 
Outpatients <math>\geq</math> 18 years presenting to Cleveland Clinic Health System in Ohio and Florida who test positive for COVID-19 having any of the following symptoms
 
 
1. Fever or chills
 
2. Shortness of breath or difficulty breathing
 
3. Cough
 
4. Fatigue
 
5. Muscle or body Aches
 
6. Headache
 
7. New loss of taste
 
8. New loss of smell
 
9. Congestion or runny nose
 
10. Nausea
 
11. Vomiting
 
12. Diarrhea
 
 
Women of child bearing potential:
 
 
1. have had a menstrual period within the past 30 days, or
 
2. have had previous sterilization, or
 
3. are perimenopausal (less than 1 year) who have a negative pregnancy test, or
 
4. women of childbearing potential who do not meet the above and have a negative pregnancy test.
 
 |
| Exclusion Criteria | 
Patients who are found to be positive during hospitalization
 
Patients who reside outside Ohio or Florida.
 
Pregnant women:
                                                                                                                                                                                                                                                                                                                                                                                                                                                                                                                                                                                                                                                                                                                                                                                                                                        |

|                           |                                                                                                                                                                                                                                                                                                                                                                                                                                                                                                           |
|---------------------------|-----------------------------------------------------------------------------------------------------------------------------------------------------------------------------------------------------------------------------------------------------------------------------------------------------------------------------------------------------------------------------------------------------------------------------------------------------------------------------------------------------------|
|                           | 
Current known pregnancy
 
Positive pregnancy test (women of child bearing potential who have not had previous sterilization as defined as hysterectomy or tubal ligation)
 
Women of childbearing potential who do not meet the above criteria, last menstrual period greater than 30 days and have a positive pregnancy test.
 
Lactating Women
 
End stage kidney disease
 
Advanced liver disease awaiting transplant
 
History of Calcium Oxalate kidney stones.
 |
| Duration of Participation | Approximately 4 weeks after enrollment                                                                                                                                                                                                                                                                                                                                                                                                                                                                    |
| Study Centers             | Cleveland Clinic Main Campus Cleveland, Ohio and Florida including Satellite/ Regional Healthcare Facilities                                                                                                                                                                                                                                                                                                                                                                                              |
| Primary Endpoint          | Duration of symptoms from coronavirus 2019 including fever or chills, shortness of breath or difficulty breathing, cough, fatigue, chills, muscle or body aches, headache, new loss of taste, new loss of smell, congestion or runny nose, nausea, vomiting and/or diarrhea.                                                                                                                                                                                                                              |
| Secondary Endpoints       | Need for prescription medication, need for ER visits, need for hospitalization, side effects from supplementation                                                                                                                                                                                                                                                                                                                                                                                         |

55

## 56 1.0 INTRODUCTION

### 57 **1.1 Purpose of this Study:**

58 The purpose of this study is to examine the impact of ascorbic acid (vitamin c) and zinc  
59 gluconate in reducing duration of symptoms in patients diagnosed with coronavirus disease 2019  
60 (COVID-19). Patients above the age of 18 who present to the Cleveland Clinic (Ohio & Florida)  
61 emergency room or outpatient testing and receive a positive test for COVID-19 who are  
62 remaining in the outpatient setting for treatment, will be invited to participate in the study and  
63 included if they consent to participate. They will be randomized to receive either ascorbic acid,  
64 zinc gluconate, combination of ascorbic acid and zinc gluconate supplements or standard of care

(none of these additional supplements). These supplements will be given to patients for a duration of ten days as a part of the study. Patients will be asked to track their symptoms of systemic illness on a daily basis.(Appendix A: Symptom Assessment Tool). We will track 12 symptoms on a scale of 0-3 as follows: A) Temperature Scale (if patient has a thermometer): 0 =  $\leq 98.6$ , 1 =  $> 98.6 - 100.6$ , 2 =  $> 100.6 - 102.6$ , 3 =  $> 102.6$ ; If no thermometer: 0= No fever & no chills, 1= No fever & chills, 2= Fever & no chills, 3= Fever & chills B) Cough Scale: 0 = no cough, 1 = mild, 2 = moderate, 3 = severe C) Shortness of breath: 0 = no shortness of breath, 1 = with moderate intensity exercise 2 = with walking on flat surface 3 = short of breath with getting dressed or daily activities D) Fatigue: 0 = No fatigue/energetic, 1=mild fatigue, 2=moderate fatigue, 3=severe fatigue E) Muscle or body aches: 0 = No muscle or body aches, 1=mild muscle or body aches, 2=moderate muscle or body aches, 3=severe muscle or body aches. F) Headache: 0 = No headache, 1=mild headache, 2=moderate headache, 3=severe headache G) New loss of taste: 0 = No loss of taste, 1=mild loss of taste, 2=moderate loss of taste, 3=severe loss of taste H) New loss of smell: 0 = No loss of smell, 1=mild loss of smell, 2=moderate loss of smell, 3=severe loss of smell I) Congestion or runny nose: 0 = No congestion or runny nose, 1=mild congestion or runny nose, 2=moderate congestion or runny nose, 3=severe congestion or runny nose J) Nausea: 0 = No nausea, 1=mild nausea, 2=moderate nausea, 3=severe nausea K) Vomiting: 0 = No vomiting, 1=mild vomiting, 2=moderate vomiting, 3=severe vomiting L) Diarrhea: 0 = No diarrhea, 1=mild diarrhea, 2=moderate diarrhea, 3=severe diarrhea. Each patient will have a composite score ranging from 0-12/day. The tracking will continue for the 28 days of study participation for each subject. They will also be asked to complete a questionnaire at the beginning of study period, day 7, day 14, day 21 and day 28. The purpose of the

questionnaire is to assess whether patient received additional medications/ supplements, sought treatment at emergency rooms or were hospitalized, or experienced side effects from the study supplements.

The primary clinical endpoint is the number of days required to reach a 50 percent reduction in the cumulative 0-36 score from the four symptom categories. For secondary endpoints we will assess a) the number of days required to reach a score of 0 b) total composite score at day 5 of the supplementation, c) differences in emergency room visits and d) differences in hospitalizations e) differences in severity of symptoms between study arms f) differences in number of patients who were prescribed adjunctive medications for their diagnosis, and g) differences in number of patients in study arms who experienced side effects from the supplements.

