## **2.0 Study Design, Objective, and Clinical Endpoints**

This is a prospective, randomized study which plans to enroll 520 patients with a principal diagnosis of COVID-2019, managed in an outpatient setting, who presented after being sent by a healthcare provider to get tested and receive a PCR-assay based confirmed diagnosis of the disease. All patients who agree to participate in the study will answer a baseline questionnaire about their symptoms at the time of inclusion. Patients will then be randomized to one of 4 study arms. Patients in Arm A (n=130) will receive 8000 mg of vitamin C (to be taken divided over 2-3 times a day with meals) for 10 days after positive diagnosis. Patients in Arm B (n=130) will receive zinc gluconate 50 mg for 10 days, to be taken at bedtime, after positive diagnosis. Patients in Arm C (n=130) will receive 8000 mg of vitamin C (to be taken divided over 2-3 times a day with meals) and zinc gluconate 50 mg for 10 days (taken at bedtime). Patients in Arm D (n=130) will not receive any of the study medications and continue on standard of care.

Patients will then track their symptoms daily from day 0 to day 28 answering 12 basic questions on illness severity. Symptom assessment tools will be completed by patients daily either electronically or on paper. For those completing the tool electronically a tool will be emailed to the patient daily via RedCap. For those completing the tool on paper a 28 day paper assessment tool will be provided to the patient at the time of consent via email/courier/text/express mail. For those patients completing a paper tool, a research staff member will contact the patient daily via phone call to obtain their daily assessment scores. Study team members will call patients at days 7, 14, 21, and day 28 of the study period to obtain information regarding hospitalizations, ER visits, additional medications prescribed by a healthcare provider

or over the counter, and any side effects from the study supplements that the patient could have experienced. Study team members may also call patients if non-compliance with completion of the daily symptom assessment tool.

Patients seen in the Emergency Department (ER) during the course of study participation will continue to take study supplement(s) (if within the initial 10 days) and continue daily symptom assessments as above.

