## **2.1 Primary Objective**

The primary objective will be evaluating the duration of symptoms in the four study arms. We will assess this by counting from when peak symptom score is achieved to when there is a 50% reduction in the symptom severity score.

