## 232 **5.0 Statistical Analysis and Endpoints**

### 233 **5.1 Sample Size:**

234 This randomized control trial will aim to prospectively enroll 520 patients who have  
 235 received a positive confirmed diagnosis of coronavirus 2019. All patients will be followed for 28  
 236 days to review vital status, hospitalizations, emergency room visits, and need for additional  
 237 treatment. We assumed the standard of care group will have a 50% reduction of symptom  
 238 severity in approximately  $6 \pm 3$  days, and that at least one of the other 3 study groups will reach a  
 239 50% reduction in  $5 \pm 3$  days. When the sample size in each of the 4 groups is 130, a one-way  
 240 analysis of variance will have 80% power (2-sided alpha of 0.05) to detect a difference in means  
 241 characterized by a variance of means, V, of 0.188, assuming that the common standard deviation  
 242 is 3 days. Our study aims to enroll 520 patients to account for study drop out as well.

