### 243 **5.2 Primary Endpoints**

244 The primary endpoint will be the number of days required to reach a 50% reduction in the  
 245 symptom severity score from peak symptom score.

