### 246 **5.3 Secondary Endpoints**

247 Additional endpoints to be considered include:

248 A) Number of days required to reach a total score of 0

B) Individual severity of illness scores (fever, cough, shortness of breath, fatigue)

C) Cumulative severity score at day 5 of the study

D) Emergency room visits

E) Hospitalizations

F) Adjunctive prescribed medications

G) Side effects of supplementation

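### Section 1.1 contradicts itself on which symptoms make up the primary-endpoint score: neither 12 symptoms on 0-12 nor four categories on 0-36 fits the 0-3 item scale

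*Protocol*

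**What the plan says.** Section 1.1 introduces the diary with "We will track 12 symptoms on a scale of 0-3 as follows" and lists items A to L, each with its own 0-3 scale. It then states: "Each patient will have a composite score ranging from 0-12/day". Its next paragraph sets the primary clinical endpoint as the number of days to a "50 percent reduction in the cumulative 0-36 score from the four symptom categories".

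Other places bear on which symptoms are meant:

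- The Primary Endpoint row of the synopsis describes duration of symptoms and names all 12, but mentions no score.
- Section 2.0 has patients "answering 12 basic questions on illness severity" each day, and the symptom assessment tool has 12 rows and 12 scale keys.
- Section 2.1 assesses the primary objective by "counting from when peak symptom score is achieved to when there is a 50% reduction in the symptom severity score".
- Section 5.2 takes the reduction in the "symptom severity score from peak symptom score". Like Section 2.1, it gives no item list and no range.
- Section 5.3 B lists a secondary endpoint, "Individual severity of illness scores (fever, cough, shortness of breath, fatigue"), which is the only place where four symptoms are named as a set.

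**The concern.** Only one sentence in the protocol gives the primary score both an item set and a range, and the two do not agree. A programmer who follows the words *four symptom categories* would sum four items. One who follows the figure 0-36 would sum twelve. Sections 2.1 and 5.2 cannot settle it, because they refer to a score without saying what is in it.

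The two sums can give the same patient different days to a 50% reduction. They can also give different days to a score of 0 and different day-5 scores. The trial is open label and the scores are patient-reported, so the item set should not remain open to choice once data have been seen.

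**Working it through.** **Inputs from the protocol.** Each item is scored 0-3 and there are 12 items (Section 1.1 and the diary). The stated ranges are 0-12 per day and 0-36 (Section 1.1). The reduction is 50% from the patient's own peak (Sections 2.1 and 5.2).

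**Ranges.** Maximum total = number of items × maximum per item.

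| Items summed | Maximum | Range stated in Section 1.1 |
|---|---|---|
| 12 symptoms | 12 × 3 = 36 | 12 |
| 4 categories | 4 × 3 = 12 | 36 |

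Neither stated range is reproduced, and each fits the other item set. Twelve items scored present/absent would give 12 × 1 = 12, but the protocol scores every item 0-3.

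**Does the range label matter?** No. The threshold is half of the patient's own peak, so the nominal maximum does not enter the calculation. Only the set of items summed does.

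**Does the item set matter?** If all symptoms fall in proportion, both sums halve on the same day and the difference is zero. The two patients below are invented, and all their scores are assumptions.

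*Patient 1.* The four core symptoms (fever, cough, shortness of breath, fatigue) total 8 at peak and fall 1 point per day. Taste and smell stay at 3 each, and the other six items are 0.
- Four items: half of 8 is 4. 8 − 4 = 4, reached on day 4.
- Twelve items: the peak is 8 + 6 = 14 and half is 7. The core part must be 7 − 6 = 1, and 8 − 7 = 1 is reached on day 7.
- Difference: 7 − 4 = 3 days.
- Day-5 score: 8 − 5 = 3 on four items, 3 + 6 = 9 on twelve.
- Score of 0: day 8 on four items; not reached on twelve while taste and smell loss persist.

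*Patient 2.* The core symptoms ease over days 3 to 5, and taste and smell loss stay severe to day 11. Daily totals from day 0, which is the first day at peak:
- Four items: 7, 7, 7, 5, 3. Half of 7 is 3.5, first met on day 4.
- Twelve items: 14, 14, 14, 12, 9, 8, 8, 8, 8, 8, 7. Half of 14 is 7, first met on day 10.
- Difference: 10 − 4 = 6 days.

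**Sample size.** Section 5.1 plans in days: means of 6 and 5, SD 3, 130 per arm, and "analysis of variance will have 80% power (2-sided alpha of 0.05) to detect a difference in means".
- For means 6, 5, 5, 5 the grand mean is 5.25, so V = (0.75² + 3 × 0.25²)/4 = 0.1875, which rounds to the stated 0.188.
- The noncentrality is 520 × 0.188/3² = 10.86. The noncentral F distribution then gives 79.5% power at 130 per arm, and 132 per arm for 80%.

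This agrees with the plan to within rounding. No input depends on the score's items or range.

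**The case against.** The strongest reply is that the intended meaning is plain. The synopsis names 12 symptoms, the inclusion criteria list the same 12, patients answer 12 questions, the diary has 12 rows, and the figure 0-36 can come only from 12 items. On that reading, the 0-12 range and the four categories are leftovers from an incomplete update. Most of this stands. A reader might infer that a four-symptom 0-12 score and a 12-symptom 0-36 score are equally live as primary scores. The protocol does not support that: no sentence pairs four symptoms with a 0-12 primary score, and the weight of the text favours twelve. What remains is that the intended score has to be inferred, and the one sentence that defines it says otherwise.

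One could also try to rescue that sentence by supposing that the 12 items are grouped into four categories. The protocol defines no such grouping, and it would leave the 0-12 range wrong.

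Section 5.3 B might be read as proof that the total has four items. It is weak evidence, because it concerns individual symptom scores. Reporting four of those is compatible with a 12-item total, so it need not be extended to all 12.

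Finally, an SAP not available here may fix the scoring algorithm. That would reduce the risk of a later choice, but it would not remove the contradiction from the protocol.

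**Conclusion.** The definition of the primary-endpoint score in Section 1.1 is wrong as written and should be corrected. The arithmetic needs no assumption: 12 × 3 = 36 and 4 × 3 = 12, so both stated pairings fail. The rest of the document points to a 12-item total of 0-36 without stating it for the primary endpoint.

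The size of the consequence depends on how long the non-core symptoms last. It is zero if symptoms fall in proportion, and 3 and 6 days in the two invented patients. The protocol gives no data from which to estimate a typical value.

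A reader might set those figures against the planned difference of 6 − 5 = 1 day and infer that the item set could swamp the treatment effect. That comparison is not like for like. The 3 and 6 days are shifts within one patient that could occur in every arm, whereas the 1 day is a difference between arm means. A shift common to all arms does not bias that difference, and no effect on the treatment comparison has been shown.

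**What to change.** - **Section 1.1, composite range:** change the daily range to 0-36/day (12 symptoms × 0-3).
- **Section 1.1, primary endpoint:** replace the reference to four categories with *the 12 symptoms*. Add *from peak score*, which Sections 2.1 and 5.2 use and this sentence omits.
- **Sections 2.1, 5.2, 5.3 A and 5.3 C:** name the score each time as the 12-symptom 0-36 total.
- **Section 5.3 B:** may stay as four individual symptom scores if that is intended.

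The cost is protocol wording only. The diary already collects all 12 items, and the sample size stands. The change should be made before outcome data are examined.
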